## Abstract

**Background:**

Most fibromyalgia patients are seen in primary care (PC). However, the effectiveness of the treatments prescribed by general practitioners is usually minimal. The main objective of the present research is to assess the efficacy of structured psycho-educational intervention, combined with relaxation, developed to improve the quality of life of patients suffering fibromyalgia (FM). The second objective is to assess the cost-effectiveness of this multimodal intervention.

**Method/Design:**

*Design*. Randomized controlled trial with a 12-month follow-up involving two groups, one of which is the intervention group that includes patients receiving a psychoeducational program and the other the control group consisting of patients treated for FM in the usual way.

*Setting*. Three urban PC centers in the province of Barcelona (Spain).

*Sample*. The total sample comprises 218 patients (over 18 years of age) suffering FM, selected from a database (Rheumatology service-Viladecans Hospital) of patients with this illness. Only those patients introduced in the database between the years 2005 and 2007 were included in the selection. Selected patients will be asked for written informed consent to participate in the study.

*Intervention*. Multi-component program including information about the illness, counselling about physical exercise and training in autogenic relaxation. The intervention consists of nine 2-hour sessions delivered during a two-month period. The pharmacological treatment prescribed by the physician was maintained in both groups.

*Main variables*. Sociodemographic characteristics, quality of life, use and cost of healthcare and social services.

*Measures*. Quality of life is to be measured with the FIQ and the EuroQol-5D, and the use of healthcare services with an adapted version of the Client Service Receipt Inventory (CSRI). These variables will be measured before the beginning of the program (baseline) and 1, 2, 6 and 12 months later.

**Discussion:**

This research project is an attempt to demonstrate that a psycho-educational program implemented in the context of PC can produce a significant increase in the quality of life for patients with FM, as well as a decrease in the use of healthcare and social services, compared with usual care.

**Trial registration:**

NCT00550966

## Background

Fibromyalgia (FM) is a chronic illness of unknown origin that provokes intense widespread pain and fatigue and affects people in the biological, psychological and social dimensions [1-3]. The diagnosis of FM is mainly clinical and the practitioner takes into account patient history, physical examination and laboratory evaluations. The American College of Rheumatology (ACR) established two major diagnostic criteria in 1990 [4]: first, a history of widespread pain for at least three months, and second, patient reporting of tenderness in at least 11 of 18 defined tender points when digitally palpated with about 4 Kg per unit area of force. The absence of reliable diagnostic tools has generated the need for employing subjective scales to assess the pain and fatigue of these patients [2].

The prevalence of FM in the general population is about 2–4%, and it is nine times more frequent in women than men [1,3]. In PC consultations the prevalence is about 5–7% [5]. Given its high prevalence and morbidity, patients suffering FM present an elevated frequency of use index for healthcare resources.

Although the aetiology of FM is still unknown, it is probably multifactorial [6-9], which is why multidisciplinary and biopsychosocial approaches usually obtain better outcomes than symptomatic treatment alone [10-13]. The main goal of most treatments is to reduce muscular dysfunction and functional impotence caused by pain. Among pharmacological treatments, only a minority has demonstrated significant efficacy. As far as we know, there is evidence of the efficacy of amitriptyline and cyclobenzaprine, whereas studies focused on the efficacy of tramadol and selective serotonin re-uptake inhibitors have yielded only modest evidence [14].

Non-extenuating physical exercise and some relaxation therapies can also increase pain tolerance, producing a global improvement in the quality of life of fibromyalgia patients [15,16]. Gowans et al [16] assessed physical functioning and mood state 6 and 12 months after the beginning of a supervised aerobic physical exercise program. These authors observed an improvement in participants' health when the program finished and 6 months later. Taggart et al [17] reported a satisfactory and significant increase in the quality of life of fibromyalgic patients after a 6-week relaxation program.

Another key component in current treatment of FM is the education of patients concerning their illness [18-20]. The main objective of educational programs is to increase skills in coping and healthy behaviour on the part of patients suffering FM. Scientific evidence has demonstrated that intensive education programs (between 6 and 17 sessions) improve pain symptoms, fatigue, insomnia and quality of life. These improvements continue 3 and 12 months later [14]. Furthermore, educational programs increase patient autonomy, reducing at the same time the consumption of medicines and use of healthcare services. The total cost of the continuous use of healthcare services by FM patients has not been estimated in Spain, but data from the USA reveal an annual cost of $2,274 per patient.

To date, it has not been demonstrated in Spain whether a multimodal program, combining autogenic relaxation and active healthcare education, produces a significant improvement in the quality of life of patients with FM. In addition, we do not know whether a multimodal program is more cost-effective than the treatment usually provided to these patients.

With this background, then, the main objective of the present research project will be to determine whether a multi-component psycho-educational program for treating FM leads to better quality of life (measured with the FIQ and the EuroQol-5D) at 1, 2, 6 and 12 months, than the usual care provided in Catalan Primary Health Care. The specific aims are to assess the degree of pain perceived by fibromyalgia patients attending the multimodal program, as well as the total direct costs (medication consumption and visits to public or private healthcare professionals) and indirect (work days lost), and cost-effectiveness associated with this psychoeducational intervention, compared to usual care.

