**Month 2**
• FIQ
• Sociodemographic variables: 1 question (current work situation)
• Pharmacological and non-pharmacological treatment received during the last month

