### Statistical analyses

Data collected will be analysed using SAS statistical analysis software (SAS Institute Inc. 1999. v8.0, 4th ed) and employing both quantitative and qualitative techniques.

First, the intervention and control groups will be compared in order to verify that there are no significant differences between them in socio-demographic terms, clinical baseline data, etc. We shall use mean and standard deviation (SD) in continuous variables and percentages in categorical variables. For comparisons we shall use the Student-T test for continuous variables and the Chi-square test for categorical variables. Non-parametric tests may also be used.

Given that we have one between-groups factor with two levels (2 Groups: Intervention and Control) and one within-subjects factor with five levels (Baseline and 4 follow-up assessments: 0, 1, 2, 6, and 12), a 2 × 5 mixed factorial ANOVA will be performed to study the effect of the psycho-educational program on the quality of life. Then, between-subjects planned comparisons may also be used (post-hoc comparisons with independent samples T-test). If we observe differences between groups in quality of life prior to treatment, one-way analyses of covariance will be carried out using baseline scores as a covariate). In addition, we shall carry out a logistic regression analysis taking the groups as dependent variable (the target variable is a categorical variable with two categories: Intervention and Control) and the collected measures as independent variables. This analysis will let us to know the association between the intervention and the cost of the healthcare resources, controlling for the rest of variables.

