As the duration of the study is only 12 months, neither costs nor outcomes are subject to discounting [26]. Treatment costs during 12 months follow-up will be modelled by a multivariate gamma regression with a log link. Gamma modelling has been suggested as a suitable choice for analysing cost data, taking into account the skewing of the distribution of the cost data [27,28]. QALYs gained in the first and last six months after the beginning of the program will be approximated by measuring the area under the curve (Figure 1).

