**Figure 1 F1:**
[figure not shown]
Formulas for calculating the QALYs gained in the first and last six months after the beginning of the program.

In the Figure 1, d_0–6 _is the incremental treatment effect on change in EQ-5D utility score for the first 6 months and d_6–12_the incremental treatment effect on change in EQ-5D utility score for the last 6 months. These incremental treatment effects will be estimated using multivariate ordinary least squares regressions, adjusting for baseline differences among treatment groups. The covariates included in the models will be: age, gender, years of education, employment and marital status, baseline FIQ and EQ-5D utility scores, and type of medication prescribed. To address uncertainty in the ICUR sampling distribution, non-parametric bootstrapping with five thousand replications will be carried out for each treatment comparison [29].

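### EQ-5D is promised at months 1, 2, 6 and 12 but scheduled only at months 6 and 12, so two of the eight comparisons in the main objective have no data and the QALY area has no point near program end

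*Protocol article*

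**What the plan says.** The Background section states the main objective as showing that the program "leads to better quality of life (measured with the FIQ and the EuroQol-5D) at 1, 2, 6 and 12 months", compared with usual care. The abstract agrees. It says "Quality of life is to be measured with the FIQ and the EuroQol-5D", adds the CSRI for service use, and continues: "These variables will be measured before the beginning of the program (baseline) and 1, 2, 6 and 12 months later".

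Table 1 sets out the content of each follow-up visit. Months 1 and 2 each have three entries: the FIQ, one question on work situation, and "Pharmacological and non-pharmacological treatment received during the last month". EQ-5D and the CSRI appear only under months 6 and 12. Table 1 has no baseline row, but the cost-utility section lists "baseline FIQ and EQ-5D utility scores" among its covariates, so a baseline EQ-5D is implied.

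Two analyses depend on this schedule. Under Statistical analyses, "a 2 × 5 mixed factorial ANOVA will be performed to study the effect of the psycho-educational program on the quality of life", with "one within-subjects factor with five levels (Baseline and 4 follow-up assessments: 0, 1, 2, 6, and 12" as the time factor. Under Cost-utility analyses, "QALYs gained in the first and last six months after the beginning of the program will be approximated by measuring the area under the curve". The text to Figure 1 defines two incremental utility effects, one for months 0–6 and one for months 6–12.

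**The concern.** The objective and the abstract promise EQ-5D measurements that the visit schedule does not collect. An article may leave detail to a fuller document, but this is not such a case. Table 1 lists each visit item by item and names EQ-5D where it is given, so its absence at months 1 and 2 is a stated schedule.

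Three things follow. First, the EQ-5D part of the main objective has no data at months 1 and 2, and utilities not collected then cannot be recovered later. Second, the article uses the term quality of life for both instruments, but a five-level time factor fits only one of them. Third, the program runs for two months, so the month 2 visit falls at about its end. With utilities at 0, 6 and 12 months only, the area under the curve assumes a straight line from baseline to month 6. QALYs gained are the denominator of the ICUR, so any departure from that line carries through to the cost-utility result. If the sections are left unreconciled, it is also open which EQ-5D time points belong to the main objective.

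**Working it through.** **1. Does the sample size depend on this?** Inputs from Setting and study sample: difference of 5 FIQ points, 12.1 (called a standard error, read here as an SD), two-sided alpha 0.05, power 0.80, dropout 15%.

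n per arm = 2 × [12.1 × (1.960 + 0.842) / 5]² = 91.9, rounded up to 92. With dropout: 92 / 0.85 = 108.2, rounded up to 109. This reproduces the stated 109 per condition. It rests on the FIQ alone, so the EQ-5D schedule does not affect it.

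**2. Promised against scheduled follow-up measurements.**

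| Instrument | Month 1 | Month 2 | Month 6 | Month 12 |
|---|---|---|---|---|
| FIQ, promised | yes | yes | yes | yes |
| FIQ, Table 1 | yes | yes | yes | yes |
| EQ-5D, promised | yes | yes | yes | yes |
| EQ-5D, Table 1 | no | no | yes | yes |

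EQ-5D: 2 of 4 follow-up visits are missing (50%). Main objective as a whole: 2 of 8 instrument-by-visit comparisons are missing (25%). With baseline, EQ-5D has three time levels (0, 6, 12) and the FIQ has five.

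**3. Effect on the QALY area.** Let d2 and d6 be the between-group utility differences at months 2 and 6. Assume no difference at baseline, month 1 at half of month 2, and month 12 equal to month 6. Trapezoid areas for months 0–6, in years:

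- Five-point schedule: [d2 + 2(d2 + d6)] / 12 = (3·d2 + 2·d6) / 12
- Baseline and month 6 only: 3·d6 / 12
- Five-point minus planned: (3·d2 − d6) / 12 = 0.25 × (d2 − d6/3)

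Months 6–12 contribute d6/2 under either schedule. The planned curve is therefore too low when d2 is more than a third of d6, exact when it equals a third, and too high when it is less.

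With D as the size of the effect (assumed shapes; the documents give none):

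| Shape | d2 | d6 | Five-point gain | 0/6/12 gain | Planned curve is |
|---|---|---|---|---|---|
| Reached by month 2, sustained | D | D | 11/12 = 0.917D | 9/12 = 0.750D | 18% too low |
| Half faded by month 6, then held | D | D/2 | 7/12 = 0.583D | 4.5/12 = 0.375D | 36% too low |
| Gone by month 6 | D | 0 | 3/12 = 0.250D | 0 | entire gain missed |
| Linear to month 6, then held | D/3 | D | 9/12 = 0.750D | 9/12 = 0.750D | exact |
| Starts after month 2, D at month 6 | 0 | D | 8/12 = 0.667D | 9/12 = 0.750D | 12.5% too high |

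With incremental cost held fixed, the size of the ICUR changes by the ratio of the two gains. It is 22% too high in the first row (0.917/0.750) and 56% too high in the second (0.583/0.375). It is undefined in the third, unchanged in the fourth, and 11% too low in the fifth (0.667/0.750 = 0.889).

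**The case against.** The best defence is that the plan works as Table 1 has it. The FIQ drives the sample size and is measured at every visit. The Statistical analyses section names no instrument for the five-level ANOVA, and that analysis runs as written on the FIQ. The cost-utility section has its own analysis of EQ-5D utilities in two six-month segments. These match the EQ-5D visits and the CSRI cost windows, and the section calls the area an approximation. On this view the Background and the abstract are loosely worded, and a text correction is enough.

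Most of this stands, and it rules out several stronger readings:

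- A reader might infer that half of the main objective is unanswerable. Half is true of the EQ-5D part only; of the objective as a whole it is a quarter.
- A reader might infer that the ANOVA section is wrong. It needs only to say which instrument it covers.
- A reader might infer that the QALY plan contradicts itself. It is coherent with EQ-5D at 0, 6 and 12 months.
- A reader might infer that the QALY gain will be understated. That holds for front-loaded effects, but the error is zero on a linear path and reverses for a late effect. The Background cites benefit at the end of an exercise program and six months later, and lasting improvement after intensive education. That leans towards the sustained shape, but it is not evidence on EQ-5D in this trial.

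What the defence does not remove is the conflict itself. The main objective, as written, still claims comparisons for which no data will be collected.

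**Conclusion.** The objective and the abstract conflict with Table 1 on when EQ-5D is measured. As scheduled, the EQ-5D comparison at months 1 and 2 cannot be made, and the 2 × 5 ANOVA applies to the FIQ only. The FIQ comparison and the 109 per arm are unaffected.

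The QALY consequence is possible but not established. It runs from missing the whole gain, through 36% and 18% too low and no error, to 12.5% too high, depending on a utility path that the documents do not give. These figures rest on the assumed shapes in the working, and on reading the planned area as a trapezoid through 0, 6 and 12 months. The Figure 1 formulas are not visible, so that reading comes from the surrounding text. The point deserves correction because it concerns the main objective and the remedy is cheap.

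**What to change.** **Preferred.** Add EQ-5D to the month 1 and month 2 rows of Table 1 and compute the area under the curve from all five points (0, 1, 2, 6, 12). Redefine the 0–6 month utility effect in the text to Figure 1 to match, for example by regressing each patient's own area for that period on group and the listed covariates. The bootstrap then uses the revised estimate. The cost is a few minutes at two interviews that already take place, and a revised QALY formula and regression. The sample size does not change.

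**If the visits cannot be changed.** Limit the EQ-5D objective to months 6 and 12 in the Background and the abstract. State under Statistical analyses that the five-level ANOVA applies to the FIQ and that EQ-5D is analysed on 0, 6 and 12 months. Note under Cost-utility analyses that the first-half area assumes a linear path from baseline to month 6, so an early effect may be missed or a late one overstated. This costs only wording, but the EQ-5D information at program end is given up.

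**Either way.** Correct the abstract's timing sentence for the CSRI, which Table 1 also gives only at months 6 and 12.

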### Variables and instruments of measurement

The study protocol was approved by the research ethics committee of the Foundation Jordi Gol i Gorina (Barcelona) and consists of the following materials:

1. *Sociodemographic characteristics*: Gender, birth date, address, marital status, education level, work status.

2. *History of the illness*: age of onset, date of the first diagnosis, pharmacological treatments (oral antidepressants, benzodiazepines-hypnotics, muscular relaxants and non-steroid analgesic and anti-inflammatory medications) and non-pharmacological treatments (physical exercise, relaxation techniques, cognitive-behavioural therapy) received during the previous 6 months.

3. *Questionnaire on chronic medical condition*.

4. *Fibromyalgia Impact Questionnaire (FIQ-Spanish version) *[23]: Instrument that measures physical function, work, and well-being, and contains visual analogue scales (VAS) for pain, sleep, fatigue, stiffness, anxiety and depression. A total score may be obtained after normalization of some items (between 0–10) and adding them to the VAS. Total scores range between 0–80 (without job items), with a higher score indicating a negative impact.

5. *EuroQoL-5D questionnaire (EQ-5D – Spanish version) *[22]: Generic instrument of health-related quality of life. It has two parts: Part 1 records self-reported problems in each of five domains: mobility, self-care, usual activities, pain/discomfort and anxiety/depression. Each domain is divided into three levels of severity corresponding to no problems, some problems, and extreme problems. Part 2 records the subject's self-assessed health on a Visual Analogue Scale (VAS); it is a vertical 10 cm line on which the best and worst imaginable health states score 100 and 0, respectively.

6. *Client Service Receipt Inventory – adapted (CSRI – Spanish version) *[24]: questionnaire for collecting information about use of healthcare and social care services, other economic impacts (such as time off work due to illness) and socio-demographic information. The variant used in this study was designed to collect retrospective data on service utilisation during the first and last six months after the beginning of the treatment.

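### The main objective and abstract promise EQ-5D at months 1 and 2, but Table 1 schedules it at follow-up only at months 6 and 12, so the five-level ANOVA is feasible for the FIQ alone

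*Protocol article*

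**What the plan says.** **Objective and abstract.** The main objective at the end of the Background is "better quality of life (measured with the FIQ and the EuroQol-5D) at 1, 2, 6 and 12 months", compared with usual care. In the abstract, under Measures, "Quality of life is to be measured with the FIQ and the EuroQol-5D", and service use is measured with the adapted CSRI. The next sentence reads: "These variables will be measured before the beginning of the program (baseline) and 1, 2, 6 and 12 months later".

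**Schedule.** Table 1 itemises the follow-up visits. Months 1 and 2 each have three entries: the FIQ, one question on work situation, and "Pharmacological and non-pharmacological treatment received during the last month". The EQ-5D and the CSRI appear only in the lists for months 6 and 12. Table 1 covers follow-up and does not list the baseline content, but the cost-utility models adjust for "baseline FIQ and EQ-5D utility scores, and type of medication prescribed", so a baseline EQ-5D is implied.

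**Analysis.** The Statistical analyses section plans a mixed ANOVA of quality of life with "one within-subjects factor with five levels (Baseline and 4 follow-up assessments: 0, 1, 2, 6, and 12"), and names no instrument. Under Cost-utility analyses, the QALYs gained in the first and in the last six months "will be approximated by measuring the area under the curve". The text under Figure 1 defines one incremental effect for months 0–6 and one for months 6–12.

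**CSRI.** Item 6 of Variables and instruments of measurement says that the variant used was "designed to collect retrospective data on service utilisation during the first and last six months after the beginning of the treatment".

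**The concern.** The objective, the abstract and the visit schedule are all printed in the article and do not agree. If Table 1 is followed, half of the EQ-5D follow-up comparisons in the main objective will have no data, and an analyst who applies the planned ANOVA to both quality-of-life instruments will find that it cannot be fitted to one of them.

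A second, lesser matter follows from the same schedule. The programme is delivered over two months, and no utility is measured during it or at its end. The shape of the utility curve between baseline and month 6 is then assumed, and any error goes into the QALY difference, which is the denominator of the incremental cost-utility ratio.

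The CSRI has a similar mismatch. The abstract places it at baseline, whereas item 6 describes an instrument that covers only the two six-month periods after treatment starts. If item 6 is right, visits, admissions and sick leave before treatment are not recorded and cannot be used as a covariate for cost.

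**Working it through.** **1. Time points side by side.**

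| Month | EQ-5D in objective and abstract | EQ-5D in schedule | FIQ in schedule | ANOVA level |
|---|---|---|---|---|
| 0 | yes (abstract) | implied by covariate list | baseline score, also a covariate | yes |
| 1 | yes | no | yes | yes |
| 2 | yes | no | yes | yes |
| 6 | yes | yes | yes | yes |
| 12 | yes | yes | yes | yes |

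The FIQ has all 5 levels. The EQ-5D has 3 (0, 6, 12), so 2 of its 4 promised follow-up points are absent and only a 2 × 3 layout is possible.

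**2. The plan's own figure.** The document gives no figure for the EQ-5D. The one computed figure it states is the sample size, which rests on the FIQ: 2 × 12.1² × (1.960 + 0.842)² / 5² = 91.9, so 92 per group, and 92 / 0.85 = 108.2, so 109. This matches the stated 109, with 12.1 read as a standard deviation. The present point does not affect it.

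**3. QALY inputs.** The planned intervals are 0–6 and 6–12 months, which need utilities at 0, 6 and 12. Table 1 plus the implied baseline score supplies these. The Figure 1 formulas are not visible, so the trapezoid rule is my reading of an area under the curve with two intervals. The documents give no utility values, so the profiles below are assumptions.

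**4. Calculation.** For between-group utility differences u(t), the area is Σ (interval length in months) × (mean of the two end values) / 12. Let d be the difference at month 2, with half of it at month 1. Months 0–2 then contribute 1 × 0.25d + 1 × 0.75d = 1d on the five-point grid.

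- *Reached by month 2 and sustained* (0, 0.5, 1, 1, 1)d. Five points: (1 + 4 + 6)d / 12 = 0.917d. Three points: (3 + 6)d / 12 = 0.750d. Ratio 0.818, or 18% too low; within the first six months, 3d against 5d, or 40% too low.
- *Early gain that fades* (0, 0.5, 1, 0.5, 0.25)d. Five points: (1 + 3 + 2.25)d / 12 = 0.521d. Three points: (1.5 + 2.25)d / 12 = 0.313d. Ratio 0.60, or 40% too low.
- *Gone by month 6* (0, 0.5, 1, 0, 0)d. Five points: (1 + 2)d / 12 = 0.25d. Three points: 0.

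Let e be the difference at months 6 and 12.

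- *Linear rise to month 6, then level.* Both grids: (3 + 6)e / 12 = 0.750e. No error.
- *No effect until after month 2* (0, 0, 0, 1, 1)e. Five points: (2 + 6)e / 12 = 0.667e. Three points: 0.750e. Ratio 1.125, or 12.5% too high.

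For scale, with an assumed difference of 0.05 the sustained case gives 0.0375 against 0.0458 QALY, and the late-onset case 0.0375 against 0.0333.

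**5. CSRI.** Item 2 of the instrument list records pharmacological and non-pharmacological treatments over the previous six months. Item 6 starts at the beginning of treatment. Prior treatments are therefore available, but prior visits, admissions and sick leave are not, unless the abstract's baseline CSRI is in fact given.

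**The case against.** The best defence is that the plan works if each instrument is matched to its own analysis. The FIQ is the sample-size outcome, is scheduled at every follow-up and fits the 2 × 5 ANOVA. The EQ-5D has separate regression models over months 0–6 and 6–12, and the schedule supplies exactly the points they need. On that view only the wording of the objective, the abstract and the ANOVA paragraph is loose. Much of this stands: the FIQ analysis, the sample size and the QALY method can all be carried out as written. It does not remove the contradiction, because the main objective explicitly names the EQ-5D at months 1 and 2, and the ANOVA is set for quality of life, which the article defines by both instruments.

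Three stronger readings might be inferred, and the document does not support them.

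- *That the QALY curve misses the treatment period.* The 0–6 month interval contains the programme; what is lacking is a measurement inside it.
- *That QALYs are bound to be underestimated.* The direction depends on an unknown utility path. The Background makes an early gain plausible, since it reports benefit after a 6-week relaxation programme and at the end of an exercise programme. It also says that gains from education continue at 3 and 12 months, which fits a plateau better than a gain that is gone by month 6.
- *That costs cannot be adjusted for anything before treatment.* Prior treatments are recorded, and medication is one component of direct cost. In a randomised trial a baseline-cost covariate mainly adds precision, and the article does not promise one.

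**Conclusion.** The contradiction is established from the text alone: the objective and abstract promise four EQ-5D follow-up points and Table 1 provides two. As scheduled, the main objective cannot be answered for the EQ-5D at months 1 and 2, and the five-level ANOVA is feasible only for the FIQ.

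The QALY consequence is a limitation, not an inconsistency. Its size rests on assumed utility paths and on a trapezoid reading of a formula that is not shown. Across those paths the error runs from none, through 18% and 40% too low, to complete loss of a transient gain, with a modest overestimate for late onset. The CSRI mismatch between the abstract and item 6 is real, but its statistical cost is mainly lost precision in the cost comparison.

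**What to change.** **Preferred.** Add the EQ-5D to the month 1 and month 2 lists in Table 1 and compute the area under the curve over 0, 1, 2, 6 and 12 months. This meets the objective as written, supplies the five ANOVA levels and removes the straight-line assumption across the programme. The cost is a few minutes of patient time at two interviews that already take place, and an extension of the Figure 1 formulas and effect models to the added intervals.

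**Otherwise.** Limit the EQ-5D statements in the objective and abstract to months 6 and 12, name the FIQ as the outcome of the 2 × 5 ANOVA, give a 2 × 3 layout for the EQ-5D, and state that QALYs assume linear change from baseline to month 6. This costs only wording, but gives up the early EQ-5D comparisons. It is the only route for participants already past month 2.

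**CSRI.** Reconcile the abstract with item 6. Giving the CSRI at baseline for the preceding six months would honour the abstract and allow baseline service cost as a precision covariate in the gamma cost model, at the cost of one more questionnaire at the baseline interview. If that is not intended, correct the abstract.
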